**Methods:**

We will recruit 32 individuals with SCI who have been discharged from inpatient rehabilitation within the previous 3 years and their primary caregivers. Patient/caregiver pairs will be randomized to the MFG intervention or an active SCI education control (SCIEC) condition in a two-armed randomized trial design. Participants will be assessed pre- and post-program and 6 months post-program. Intent to treat analyses will test two a priori hypotheses: (1) MFG-SCI will be superior to SCIEC for SCI patient activation, health status, and emotion regulation, caregiver burden and health status, and relationship functioning, and (2) MFG will be more effective for individuals with SCI and their caregivers when the person with SCI is within 18 months of discharge from inpatient rehabilitation compared to when the person is between 19 and 36 months post discharge.

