### General analytic approach

Preliminary analyses will include inspection of descriptive statistics and features of the data to determine whether data transformations for non-normal data are necessary. We will initially test whether baseline characteristics of the study population (e.g., age, sex, race, neurological level, extent of lesion) and other variables known to be related to the primary outcomes are comparable between the two treatment groups using independent t-tests or Wilcoxon rank-sum tests for continuous variables, and chi-square or Fisher’s exact tests for categorical variables. Groups will be considered imbalanced on variables that differ at *p* < .10, and all such imbalanced baseline prognostic factors will be included in primary analyses as covariates. We intend to measure the primary and secondary outcomes described in Table 1 at three time points for each participant (SCI patient and caregiver). Because repeated measurements on individual subjects tend to be correlated and, in some cases, the number and intervals of time between observations may vary among subjects, we will analyze each outcome measure with a general linear mixed model (GLMM) for longitudinal (repeated measures) data by modeling for 3 independent variables: Group (MFG-SCI vs. SCIEC), Time Since Inpatient Treatment (0–18 months vs. 19–36 months post-treatment), and Time of Assessment (pre-treatment, post-treatment, and 6-month follow-up) with covariates represented in the analyses as necessary, and individual subject variables will be simultaneously modeled as random effects. GLMM will account for dependence in repeated measures and accommodate correlated errors, unequal correlations among time points, unbalanced data resulting from missing data points, and unequal intervals between testing occasions. All principal analyses will be conducted based on the intention-to-treat principle in which any participant randomized to a treatment arm remains in it regardless of adherence to or completion of treatment. We will measure level of participation and conduct a sensitivity analysis that assesses the stability of the conclusions from the intention-to-treat analysis against an available-case analysis that considers only data from fully-adherent participants in a General Linear Model (GLM) repeated measures analysis of variance (RMANOVA). With multiple time points and variables representing outcomes at both the individual and caregiver levels, the planned analyses involve multiple comparisons, which increases likelihood that any single outcome will be found to be statistically significant based on chance alone. In order to minimize this risk, we have carefully selected a limited number of outcomes and clearly designated primary and secondary outcomes. Accordingly, we will also employ a more stringent observed type I error criterion (*p* = .01) than the typical .05 criterion in order to buffer against potential inflation of Type I errors due to multiple tests being performed in both the GLMM and RMANOVA.

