
### Tests of specific study hypotheses

Statistical analyses will test each of our a priori hypotheses that (1) MFG-SCI will be superior to SCIEC for SCI quality of life measures (patient activation, health status), and emotion regulation, caregiver burden and health status, and relationship functioning, and (2) MFG will be more effective for individuals with SCI and their caregivers when the person with SCI is within 18 months of discharge from inpatient rehabilitation compared to when the patient is between 19 and 36 months post discharge from inpatient rehabilitation. GLMM and RMANOVA will test main effects for Group, Time since Inpatient Treatment, and Time of Measurement, as well as the Group-by-Time of Measurement and Time since Inpatient Treatment-by-Time of Measurement interactions. GLMM will also be used to estimate effect sizes for each main effect.

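### The RMANOVA on fully adherent participants is mislabelled available-case and serves both as a sensitivity analysis and as a test of the a priori hypotheses

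*Protocol article*

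**What the plan says.** Four places in the Protocol article bear on this.

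- **General analytic approach, population and roles.** "All principal analyses will be conducted based on the intention-to-treat principle", using the GLMM. The authors will then "conduct a sensitivity analysis that assesses the stability of the conclusions from the intention-to-treat analysis" by setting it against "an available-case analysis that considers only data from fully-adherent participants", fitted by RMANOVA.
- **General analytic approach, error control.** The significance level is set at .01, more stringent "than the typical .05 criterion in order to buffer against potential inflation of Type I errors". The stated reason is "multiple tests being performed in both the GLMM and RMANOVA".
- **Tests of specific study hypotheses.** After restating the two a priori hypotheses, the text says "GLMM and RMANOVA will test main effects for Group, Time since Inpatient Treatment, and Time of Measurement", together with two interactions, one of them Group-by-Time of Measurement. No order between the two procedures is given there. Only effect-size estimation is reserved for the GLMM.
- **Abstract, Methods.** "Intent to treat analyses will test two a priori hypotheses".

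Table 1 bolds three primary outcomes: the Patient Activation Measure, the Caregiver Burden Inventory and the caregiver CES-D-10.

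**The concern.** The label is wrong. An available-case analysis keeps every participant with an observed value, whereas an analysis confined to fully adherent participants is per-protocol. A reader of the results could take an adherence-selected estimate for one that uses all the data.

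The role is also unsettled. One section makes the RMANOVA a supporting check. The next lists it as a test of the hypotheses, and the alpha sentence treats its tests as part of the family to be protected. If both models test the hypotheses, the plan has two routes to a superiority claim, and one of them conditions on something that happens after randomisation. Tables 2 and 3 show that the arms differ by design in homework, group support and personal relevance, so adherence could plausibly differ by arm. The adherent subsets would then no longer be randomised groups.

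As a check on the intention-to-treat result, the RMANOVA is also hard to interpret. It changes the population and the model together, and a conventional RMANOVA drops anyone with a missing visit. A disagreement with the GLMM could come from any of these changes.

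**Working it through.** **Step 1. The roles given to RMANOVA, side by side.**

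| Place in the Protocol article | Role of RMANOVA | Participants |
|---|---|---|
| General analytic approach, sensitivity sentence | Check on the intention-to-treat result | Fully adherent only |
| General analytic approach, alpha sentence | Source of tests covered by .01 | Not restated |
| Tests of specific study hypotheses | Tests the hypotheses beside the GLMM | Not restated |
| Power calculations | Procedure for which power is computed | All 32 dyads, or 28 after attrition |

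The only definition of the RMANOVA population is the first row, so a literal reader carries it into the third. An adherent-only RMANOVA is not an intent-to-treat analysis, so the third row then conflicts with the abstract. The fourth row uses all dyads, which fits neither the definition nor a supportive role.

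**Step 2. Inputs for the error rate.** The plan gives no familywise figure to reproduce. From the article: α = .01, 3 primary outcomes, 2 tests involving Group per outcome (main effect and Group-by-Time), 32 dyads, 3 measurement times, correlation .2 among repeated measures. Assumed, because the article does not give them: independent outcomes, and 16 to 28 fully adherent dyads.

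**Step 3. GLMM alone.** With k independent tests the chance of at least one false rejection is 1 − (1 − .01)^k.

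- One Group test per primary outcome, k = 3: 1 − .99³ = 3.0 %.
- Two Group tests per primary outcome, k = 6: 1 − .99⁶ = 5.9 %.

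**Step 4. GLMM plus adherent-only RMANOVA.** The two tests of one effect share data and are correlated. If the adherent dyads are a random subset of n out of 32, the correlation of the two estimates is about √(n/32): .94 for n = 28, .87 for n = 24, .71 for n = 16. Let p be the probability that at least one of the pair rejects at two-sided .01 under the null, from a bivariate normal distribution. Over k effects the chance is 1 − (1 − p)^k.

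| Correlation | p | k = 3 (Group main effect only) | k = 6 (main effect and Group-by-Time) |
|---|---|---|---|
| .95 | .0136 | 4.0 % | 7.9 % |
| .90 | .0149 | 4.4 % | 8.6 % |
| .80 | .0166 | 4.9 % | 9.6 % |
| .70 | .0177 | 5.2 % | 10.2 % |

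**Step 5. Check by simulation.** I simulated three independent outcomes under the null with 16 dyads per arm, three times and correlation .2. RMANOVA F tests at .01 stood in for the GLMM, and the adherent subset was nested in the full set. Over both Group tests, one model gave about 6 %. Adding the adherent-only analysis gave about 8 % with 28 adherent dyads, 9 % with 24 and 10 % with 16. For the Group main effect alone the figures were about 3 % and 4–5 %.

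Steps 4 and 5 count multiplicity only, because the subset is drawn without regard to outcome. Bias from selecting on adherence would come on top. It cannot be sized, because the article gives no adherence rate.

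**The case against.** The strongest reply is that the hierarchy is already set. General analytic approach separates principal from sensitivity analyses, and the hypothesis section can be read as listing the effects fitted in each model. The .01 level was also chosen with both models in mind. Part of this stands: the first section does rank the two. But the hypothesis section, where a reader looks for the deciding test, does not repeat the ranking, and the alpha sentence treats RMANOVA as a source of tests to be protected.

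Several stronger readings are tempting, and the article does not support them.

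- *The adherent-only analysis itself breaches intention-to-treat.* It does not. The principle is applied to principal analyses, and an adherent-only check beside them is compatible with it. The conflict arises only when that check is listed as a hypothesis test.
- *The second model doubles the error rate.* It doubles the number of tests. Treating all 12 as independent gives 1 − .99¹² = 11.4 %, but the two models share data, so that figure is too high.
- *The .01 level is too lenient.* For three primary contrasts it is stricter than Bonferroni at .05 (.05/3 = .0167). If only the Group main effect is counted, both models together give about 4–5 %.
- *No other sensitivity analysis is planned, and the missing-at-random assumption goes unexamined.* A journal article may leave both to the analysis plan, as it may the definition of full adherence.
- *A Holm procedure would recover power, or delta-adjusted imputation is needed.* These are choices of method. A power gain could be stated only by fixing an effect-size metric that the article leaves open.

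Nor is the RMANOVA uninformative. Agreement with the GLMM would be weak support, and disagreement would prompt a closer look.

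**Conclusion.** The point holds as a wrong label and an unresolved role. Followed as written, the plan lets a result from adherence-selected participants support an a priori superiority claim, contrary to the abstract. That is a conflict in what is stated, not a detail left out.

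The multiplicity cost is moderate: about 6 % for the GLMM alone against about 8–10 % for both models, over three primary outcomes and two Group tests each. This rests on independent outcomes, 16–28 adherent dyads and adherence unrelated to outcome. The more serious risk is the selection itself, which the article gives no means of quantifying.

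**What to change.** - In Tests of specific study hypotheses, state that only the intention-to-treat GLMM tests the a priori hypotheses. Name in advance one Group contrast for each of the three primary outcomes. Three tests at .01 give about 3 % overall.
- In General analytic approach, replace the available-case label with per-protocol and call the adherent-only RMANOVA supportive.
- Remove RMANOVA from the hypothesis-test sentence and from the sentence justifying .01.

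The change is a few sentences. It needs no further participants, data collection or programming, provided it is made before outcome data are examined by arm.

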
### Tests of specific study hypotheses

Statistical analyses will test each of our a priori hypotheses that (1) MFG-SCI will be superior to SCIEC for SCI quality of life measures (patient activation, health status), and emotion regulation, caregiver burden and health status, and relationship functioning, and (2) MFG will be more effective for individuals with SCI and their caregivers when the person with SCI is within 18 months of discharge from inpatient rehabilitation compared to when the patient is between 19 and 36 months post discharge from inpatient rehabilitation. GLMM and RMANOVA will test main effects for Group, Time since Inpatient Treatment, and Time of Measurement, as well as the Group-by-Time of Measurement and Time since Inpatient Treatment-by-Time of Measurement interactions. GLMM will also be used to estimate effect sizes for each main effect.

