### Power calculations

No studies comparing MFG to a control condition in an SCI population exist from which to estimate power. Therefore, we have used a recent trial that included [name] as a co-investigator implementing MFG with survivors of TBI and their families [24]. Significant decreases were reported in TBI patient anger-expression, social support, and occupational activity, with caregivers reporting significantly decreased caregiver burden; all *p*’s < .05. Effect sizes across measures ranged from .6 to 1.0. The proposed study will be powered to determine whether the MFG-SCI is superior to the SCIEC control condition in 2 × 2 × 3, group-by-time since inpatient rehabilitation (0–18 months post-inpatient rehab vs. 19–36 months) by measurement time (baseline, post-treatment, 6-month follow-up) analyses of variance with repeated measures on the second factor. We have elected to estimate statistical power for the more conservative RMANOVA than for the more liberal GLMM procedure in order not to overestimate power. Given the lower bound effect size of .6, a 2-sided type I error rate of 0.01 [24], 1 degree-of-freedom for each between-groups comparison and 2 degrees-of-freedom for the repeated measures main effect, and an estimated correlation among repeated measures of 0.2, at a sample size per group of 16 (32 total dyads), the power to establish superiority of the intervention over the control condition is estimated to be 97 % across the primary and secondary endpoints for SCI patients and caregivers. If we were to lose four dyads to attrition, reducing number of dyads to 28 (14 per group), statistical power given the parameters above would be 95 %. Additionally, at a more conservative effect size of .5, at a sample size of 28, we would still have 87 % power to detect a main effect among groups. Thus, we have good power to detect a medium to large effect size even with a moderate degree of attrition. All power calculations were made with PASSv11.

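### Power and effect sizes attach to a Group main effect that includes the pre-treatment visit, and no term is named as deciding hypothesis 1

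*Protocol article*

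**What the plan says.** In the protocol article, General analytic approach puts three factors in the mixed model: Group, Time Since Inpatient Treatment, and "Time of Assessment (pre-treatment, post-treatment, and 6-month follow-up"). Pre-treatment is therefore a response level, not a covariate.

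Tests of specific study hypotheses states that "GLMM and RMANOVA will test main effects for Group, Time since Inpatient Treatment, and Time of Measurement". The same sentence goes on to list two interactions, one of them Group-by-Time of Measurement. No term is assigned to H1. On estimation, the section says "GLMM will also be used to estimate effect sizes for each main effect" and mentions no effect size for an interaction or other contrast.

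Power calculations uses a repeated-measures ANOVA whose time factor again includes baseline, with one degree of freedom for the between-groups comparison. It reports 97% power to establish superiority at 32 dyads, 95% at 28 dyads, and 87% at 28 dyads with the smaller effect size. The last figure is described as "power to detect a main effect among groups". No power is given for Group-by-Time.

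**The concern.** In a factorial model with baseline as a response, the Group main effect is the arm difference averaged over all three visits. Before treatment the arms differ only by chance, so the expected difference at that visit is zero. Including it pulls the average towards zero, and chance baseline imbalance enters the estimate as if it were treatment effect. With 16 dyads per arm, such imbalance can be appreciable.

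Two things are at stake. The power claim describes a test that would perform as stated only if the full effect were already present before treatment. The planned effect sizes would describe a quantity smaller than the treatment effect. Moreover, with no term named for H1, either the main effect or the interaction could be taken as the deciding result, although they answer different questions and have different power.

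**Working it through.** **Inputs (Power calculations).** "Given the lower bound effect size of .6, a 2-sided type I error rate of 0.01"; correlation among repeated measures ρ = 0.2; N = 32 (16 per arm) or 28 (14 per arm); "at a more conservative effect size of .5, at a sample size of 28" for the third case; three visits. The metric of the effect size is not named. The stated figures are reproduced only if it is Cohen's f, where f = d/2 for two equal groups, so f = .6 means a standardised difference of 1.2.

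**Step 1: reproduce the stated power.** For the Group main effect over m visits, λ = N·f²·m / (1 + (m − 1)ρ), tested on F(1, N − 2).

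- N = 32, f = .6, m = 3: λ = 32 × .36 × 3 / 1.4 = 24.7
- N = 28, f = .6, m = 3: λ = 28 × .36 × 3 / 1.4 = 21.6
- N = 28, f = .5, m = 3: λ = 28 × .25 × 3 / 1.4 = 15.0

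Power is 98.3, 96.1 and 85.2%, against the stated 97, 95 and 87%: all within 2 points. With only two visits (m = 2) it would be 94.0, 89.6 and 73.2%, which does not match. The published figures thus behave like a three-visit main effect with the full effect at every visit, baseline included.

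**Step 2: set the expected baseline difference to zero.** With arm effects (0, f, f), the visit average is (0 + f + f)/3 = 2f/3, so λ is multiplied by 4/9: 24.7 becomes 11.0, 21.6 becomes 9.6, and 15.0 becomes 6.7.

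**Step 3: Group-by-Time under the same effect profile.** λ = (N/4)·Σ(dⱼ − d̄)² / (1 − ρ), on F(2, 2(N − 2)). For d = (0, 1.2, 1.2), d̄ = .8 and the sum of squares is .64 + .16 + .16 = .96. At N = 32, λ = 8 × .96 / .8 = 9.6; at N = 28, λ = 7 × .96 / .8 = 8.4. For f = .5, d = (0, 1, 1) and the sum of squares is 2/3, so λ = 7 × (2/3) / .8 = 5.8.

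**Step 4: mean of the two post-randomisation visits, adjusted for baseline.** The residual variance is (1 + ρ)/2 − ρ² = .60 − .04 = .56. Then λ = N·f² / .56 on F(1, N − 3): 32 × .36 / .56 = 20.6; 28 × .36 / .56 = 18.0; 28 × .25 / .56 = 12.5.

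| Test of H1 | 32 dyads, .6 | 28 dyads, .6 | 28 dyads, .5 |
|---|---|---|---|
| Stated in the article | 97% | 95% | 87% |
| Group main effect, full effect at all three visits | 98% | 96% | 85% |
| Group main effect, no expected baseline difference | 71% | 63% | 44% |
| Group-by-Time, 2 df | 55% | 47% | 30% |
| Baseline-adjusted mean of post visits | 95% | 92% | 77% |

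**The case against.** A reader might infer that H1 is tested on the Group main effect alone. The text does not support that. Group-by-Time is listed in the same sentence, and it does isolate differential change. The Background words H1 as more improvement under MFG than under the control, which points towards the interaction. A fitted mixed model also contains visit-specific contrasts from which a treatment effect could be taken. This objection stands. What remains is that the deciding term is not named, the power belongs to the main effect, and the effect sizes are promised for main effects only. Nor does the stated 97% carry over to the interaction.

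A reader might also infer that the reported effect is always biased by exactly one third. That holds only for equal effects at post-treatment and 6 months and equally weighted visits. The article treats durability as an open question, so the fraction is not fixed. Baseline still pulls the average towards zero whenever the later effects have the same sign.

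The effect profile behind the stated power is inferred, since the article gives none, and the match in step 1 is close but not exact. The .6 could denote the visit-averaged effect. The post-treatment effect would then have to be .6 × 3/2 = .9 in f, whereas .6 is introduced as the lower bound of the effects reported in the earlier trial in traumatic brain injury.

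Finally, much lower power follows if .6 is read as a standardised mean difference: about 41% for the undiluted main effect and 16% for the diluted one at 32 dyads. Most of that fall comes from the metric, which is a separate question, so it is not counted here. Correlations other than 0.2 would be the reviewer's assumption, and none is used.

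**Conclusion.** Wrong as written. Superiority is powered on a Group main effect that includes the pre-treatment visit, the planned effect sizes attach to main effects, and no term is named as deciding H1. On the article's own inputs, dilution alone takes the main effect from the stated 97, 95 and 87% to about 71, 63 and 44%. The other listed test relevant to H1, Group-by-Time, has about 55, 47 and 30%. The article's conclusion of good power therefore holds for neither.

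These figures assume .6 and .5 are Cohen's f, ρ = 0.2 between all visits, two-sided alpha .01, an equal effect at both later visits, and complete data at the stated numbers of dyads. The documents do not support a claim that the main effect is the only test of H1, or that the loss is one third in every case.

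**What to change.** Name one contrast as the test of H1: the baseline-adjusted MFG-SCI minus SCIEC difference over the post-randomisation visits, for example the mean of post-treatment and 6 months. It can be fitted with baseline as a covariate and the two later visits as responses, or in a GLMM with baseline means constrained equal across arms. Either is defensible; the plan should state which. Report effect sizes for this contrast in place of the Group main effect, and give Group-by-Time a stated supporting role if it is kept. Restate the power for the named contrast, with the effect-size metric and the assumed effect at each visit.

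The cost is analysis wording and one recalculation. No visits, measures or participants are added, and on the inputs above the named contrast recovers most of the power claimed.

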**Discussion:**

Support for our hypotheses will indicate that MFG-SCI is superior to specific education for assisting patients and their caregivers in the management of difficult, long-term, life adjustments in the months and years after SCI, with increased efficacy closer in time to the injury.

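### None of the listed tests crosses treatment group with time since discharge, so the list as written cannot address Hypothesis 2

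*Protocol article*

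**What the plan says.** The section on tests of specific hypotheses in the protocol article opens with a commitment: "Statistical analyses will test each of our a priori hypotheses". Hypothesis 2 is then restated: "MFG will be more effective for individuals with SCI and their caregivers when the person with SCI is within 18 months of discharge", compared with 19 to 36 months.

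The tests follow, beginning with three main effects: "GLMM and RMANOVA will test main effects for Group, Time since Inpatient Treatment, and Time of Measurement". Two interactions are then added to these, and no others: "as well as the Group-by-Time of Measurement and Time since Inpatient Treatment-by-Time of Measurement interactions". Estimation is confined to main effects: "GLMM will also be used to estimate effect sizes for each main effect".

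Two other sections bear on the point:
- The general analytic approach describes the mixed model "by modeling for 3 independent variables: Group (MFG-SCI vs. SCIEC), Time Since Inpatient Treatment" and time of assessment. It names no interaction.
- The power section says "The proposed study will be powered to determine whether the MFG-SCI is superior to the SCIEC control condition in" a 2 × 2 × 3 repeated-measures analysis of variance, with time since inpatient rehabilitation as the second factor. Its power figures are for intervention versus control.

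The Discussion paragraph of the Abstract says that support for the hypotheses would show MFG-SCI to be superior, "with increased efficacy closer in time to the injury".

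**The concern.** Hypothesis 2 is a claim of effect modification: the MFG-SCI minus SCIEC difference depends on the stratum of time since discharge. Any test of it must contain both factors. That means Group × Time since discharge or, for change over visits, Group × Time since discharge × Time of Measurement. The list has neither, and the effect sizes to be estimated do not include the difference in effect between strata.

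The nearest listed term, Time since Inpatient Treatment × Time of Measurement, compares the trajectories of the two strata with the arms pooled. It asks whether recently discharged people change more, whichever programme they attended. Faster natural adjustment soon after discharge would produce that pattern without any difference in treatment effect. One of only two a priori hypotheses is therefore left without a named test, and a term that looks similar stands where a reader would expect one.

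**Working it through.** **1. What the listed terms can express.** The 2 × 2 × 3 design has 12 cell means. The listed terms use 1 (intercept) + 1 (Group) + 1 (Time since discharge) + 2 (Time of Measurement) + 2 (Group × Time of Measurement) + 2 (Time since discharge × Time of Measurement) = 9 dimensions. The other 12 − 9 = 3 are Group × Time since discharge (1) and the three-way term (2). The Hypothesis 2 contrast, (MFG-SCI − SCIEC) in the early stratum minus (MFG-SCI − SCIEC) in the late stratum, is zero on all nine listed dimensions. This holds for the mean over visits and for change from baseline.

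**2. What the stated power refers to.** Inputs from the power section: effect size .6 (or .5), two-sided alpha .01, correlation ρ = .2, N = 32 (or 28), three visits. For the Group main effect on the mean of three visits, reading the effect size as Cohen's f (the article does not name the metric):

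λ = N f² × 3 / (1 + 2ρ), F with 1 and N − 2 df

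| N | f | λ | Recomputed | Stated |
|---|---|---|---|---|
| 32 | .6 | 24.7 | 98.3 % | 97 % |
| 28 | .6 | 21.6 | 96.1 % | 95 % |
| 28 | .5 | 15.0 | 85.2 % | 87 % |

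All three agree within 2 points, so the stated figures behave as power for the Group main effect, not for a moderation test.

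**3. The pooled interaction when there is no moderation.** Assumptions: 16 dyads per stratum, compound symmetry, and an early stratum that improves d SD more than the late one at both later visits, equally in both arms. The article gives no value for d, so a range is shown, with ρ from the article's .2 up to an assumed .5. The sum of squares of the centred pattern (0, d, d) is (2/3)d², hence

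λ = (16/2)(2/3)d² / (1 − ρ), F with 2 and 56 df, alpha .01

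| d | ρ = .2: λ, P(significant) | ρ = .5: λ, P(significant) |
|---|---|---|
| 0.3 | 0.60, 2.5 % | 0.96, 3.6 % |
| 0.5 | 1.67, 6 % | 2.67, 11 % |
| 1.0 | 6.67, 36 % | 10.67, 60 % |

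**4. Precision of the right contrast.** Assumption: an even split, 32/4 = 8 dyads per cell. The article gives no split. D is the difference in treatment effect between strata, in SD units; alpha is .01.

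*Three-way term.* The difference of differences has variance 4/8 per visit in SD² units, so λ = (8/4)(2/3)D² / (1 − ρ), F with 2 and 56 df.

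*Group × Time since discharge, baseline-adjusted.* SE = √(4v/8), with v = 1 − ρ² for one later visit and v = (1 + ρ)/2 − ρ² for the mean of two; t with 27 df.

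| Test | ρ | Power at D = 0.6 | D detectable at 80 % power |
|---|---|---|---|
| Three-way, 2 df | .2 | 2.5 % | 3.0 SD |
| Three-way, 2 df | .5 | 3.6 % | 2.4 SD |
| Adjusted, one visit (SE 0.69) | .2 | 3.9 % | 2.5 SD |
| Adjusted, one visit (SE 0.61) | .5 | 4.9 % | 2.2 SD |
| Adjusted, mean of two (SE 0.53) | .2 | 6.6 % | 1.9 SD |
| Adjusted, mean of two (SE 0.50) | .5 | 7.4 % | 1.8 SD |

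**The case against.** The strongest reply is that the power section names a 2 × 2 × 3 analysis of variance, and a full-factorial fit of that design would ordinarily carry the two missing terms. The list also gives effects to be tested, not necessarily every term in the model, and the mixed-model description does not restrict interactions. This stands in part. A reader might infer that the trial can never test Hypothesis 2, or that the model forces equal effects in both strata. The documents do not support that; it would follow only if the list were the whole model. What remains is that no section names a test of Hypothesis 2, and that the section written to specify the tests gives an explicit set without it. That is a wrong list, not a detail left to an analysis plan.

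A second reply is that nothing assigns the pooled interaction to Hypothesis 2. That is correct. A reader might infer that the investigators intend to read it so, but the article does not say this. The term is a legitimate lower-order term, and misreading it is a risk, not a stated plan.

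Third, the sentence about greater efficacy nearer to injury is already conditional on support for the hypotheses. It stands in the Abstract, and the main Discussion does not repeat it. It is not a conclusion already drawn. It lacks only a link to a specific contrast.

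Finally, the article claims power only for MFG-SCI versus SCIEC, never for Hypothesis 2. Hypothesis 1, randomisation and data collection are unaffected.

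**Conclusion.** The point holds as an inconsistency within the article. A section that promises to test both hypotheses lists tests of which none can address the second, and the list does not match the three-factor design used for power. It should be corrected, because Hypothesis 2 is one of two a priori hypotheses.

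The omission itself is algebra and needs no assumption. The size of the misreading risk does. It is small if natural recovery differs by 0.3 SD between strata and substantial only near 1.0 SD, and the article gives no figure to choose between them. The precision figures rest on an even split over four cells and on correlations of .2 to .5. Across those, the difference in effects detectable at 80 % power is about 1.8–2.5 SD in a baseline-adjusted model and 2.4–3.0 SD for the three-way 2-df test. An uneven split or attrition would make this worse. Naming the right test therefore brings correct labelling and an honest interval, not a well-powered test.

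**What to change.** In the section on tests of specific hypotheses:
- Add Group × Time since discharge and Group × Time since discharge × Time of Measurement, keeping all lower-order terms, including the pooled interaction.
- Name one contrast as the test of Hypothesis 2: the three-way contrast, or Group × Time since discharge in a baseline-adjusted model.
- Report the between-stratum difference in treatment effect with its confidence interval.

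In the power section, state that the 97 % refers to MFG-SCI versus SCIEC and does not extend to Hypothesis 2. It would be sensible to add that Hypothesis 2 is estimated rather than powered.

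In the Abstract, tie the statement about greater efficacy closer to injury to the named contrast.

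The cost is a few sentences. The moderator is already a factor in the model, so no extra data, visits or participants are needed.
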